## 8. STUDY CALENDAR

Estimated start date of enrollment: 01/06/2024

Enrollment period: 6 months

Duration of subject's participation:

- 4 months for mosquito sampling study
- 1 day for seroprevalence study and questionnaire

Total estimated study duration: 1 year

Data analysis: 6 months

Data storage period: 2 years after the last publication before archiving the data base. Data will be kept at the Chulalongkorn University, 2 years after the last publication of the results estimated at 4 years after enrolment initiation and then archived. No individual data will be stored at Institut Pasteur.

## 9. STATISTICAL CONSIDERATIONS

Sample size:

Based on the preliminary data showing a difference in prevalence rates according to school centrality and environmental typology (approximately 26% vs 15%), we estimate a necessary sample size of ~210 children for each of the four typologies (Central+/Environmental+, Central+/Environmental-, Central-/Environmental+, Central-/Environmental-).

Sample size was calculated as follows [17]

$$n = (Z_{\alpha/2} + Z_{\beta})^2 \cdot [p_0(1 - p_0) + p_1(1 - p_1)] (p_0 - p_1)^2$$

Where n is the required sample size per treatment arm,  $Z_{\alpha}$  and  $Z_{\beta}$  are constants set by convention according to the accepted  $\alpha$  error and whether a one-sided or two-sided effect,  $p_0$  is the proportion sero-positive in area type 0 (ie Central + or Environment +), and  $p_1$  the proportion areas type 2 (Central – or Environment –).

Assuming a  $p < 0.05$  as acceptable and a study with 90% power, the following constant values are:  $Z_{\alpha/2} = 1.96$  and  $Z_{\beta} = 0.84$ .

Because our preliminary data indicated variation within school centrality and environmental typology, (coefficient of variation ranging from 0.6-1), we used the following formula to estimate the number of different sites for each typology.

$$\text{Site number per typology} = 1 + (Z_{\alpha/2} + Z_{\beta})^2 \cdot [p_0(1 - p_0)/n + p_1(1 - p_1)/n + k^2(p_0^2 + p_1^2)] (p_0 - p_1)^2$$

Where k is the coefficient of variation and n the number of individuals as calculated above. Using  $n=210$  and  $k=0.6$  to 1, we would need at least two and optimally three schools per environmental typology with 80-100 children per school.

Sero-positivity (as defined by the manufacturers instructions) will be analysed by logistic regression with age, sex and centrality (high vs. low) and environmental typology (Open vs Dense) as explanatory variables using R. School mosquito densities will also be included as an explanatory variable. In the subset of individuals collecting mosquitoes in the homes will be taken into account in a separate analysis. Mosquito densities will also be analysed with respect to the environmental typology and meteorological parameters.

Socio-demographic and other baseline characteristic variables of a questionnaire will be reported descriptively using counts and percentage for categorical variables and means for continuous variables. Comparison of willingness to be vaccinated and other associated factors will be performed using one-way analysis of variance. Multivariate regression analysis will be deployed to identify and understand the key factors that may be associated with the potential uptake a vaccine using generalized linear models.

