As a pilot study, prior to roll-out across Bangkok, dengue virus sero-prevalence rates were measured using the Panbio Indirect IgG ELISA on stored blood samples from 272 children aged 3-15 years from within Bangkok. These were mapped according to their homes and schools, whose environmental typology (satellite imagery for vegetation index, height and surface of buildings) and degree of centrality (services density, frequency of transportation and visits using social media data) were established (see Figures below). The association of the degree of centrality (high vs. low) and the type of environment (Open vs. densely built-up) with sero-prevalence rates was then analysed by logistic regression, taking into account the ages of the individuals.

From this retrospective study, the median (IQR) age of the samples was 10.7 (7.6-12.6) years. DENV sero-prevalence rates among children 3-9 years and 10-15 years were 6.5% and 37.2% respectively. Children going to schools characterized by an open environment or one of low centrality had much lower sero-prevalence rates (Open vs. dense: 16.8% vs. 27.1%; Low vs high centrality: 14.8% vs. 25.2%). There was no difference in sero-prevalence rates according to the degree of centrality of their homes. However, sero-prevalence rates in homes in open environments were higher (27.1% vs. 12.6%) (Fig. 3).

**Figure 3.** Sero-prevalence rates according to landscape category and centrality in children's homes and schools

[figure not shown]

Suwanbamrung et al. [14] conducted a cross-sectional study among children aged 8-13 years from 50 public schools in Kanchanadit district to assess the correlation between knowledge, attitude and practice (KAP) in dengue infection including prevention method compare between children with and without dengue infection experience using 32-items questionnaire. The study shows no significant difference in KAP mean score between the 2 groups, but the children with previous dengue infection had better preventive practice than the other group (OR 1.34, 95%CI 1.03-1.75,  $P=0.032$ ). The study also notes that most children (more than 70%) reported that their source of dengue information came from their teacher. Thus, in addition to the sero-prevalence study, we are also interested in assessing levels of KAP concerning dengue and provide more information about dengue infection and prevention, which can then be applied in their school and household.

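### Section 9 sizes the study for one factor (two levels) but assigns the result to each of four typologies, so the stated power is not that of the centrality and environment tests.

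*Protocol*

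**What the plan says.** All of the following is in protocol section 9 unless noted.

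- **Unit of n.** After the two-proportion formula: "Where n is the required sample size per treatment arm".
- **The two groups.** p0 "is the proportion sero-positive in area type 0 (ie Central + or Environment" +), and p1 is "the proportion areas type 2 (Central – or Environment" –).
- **Planning rates.** "approximately 26% vs 15"%, described as a difference by school centrality and environmental typology. The pilot in the Background section reports, by school: "Open vs. dense: 16.8% vs. 27.1%; Low vs high centrality: 14.8% vs. 25.2"%.
- **Where the result is applied.** "we estimate a necessary sample size of ~210 children for each of the four typologies".
- **Stated power.** The text reads "as acceptable and a study with 90% power", with a Z for beta of 0.84.
- **Sites.** A second formula, with the same p0 and p1 and a coefficient of variation k of 0.6 to 1, is said to give two to three schools per typology with 80 to 100 children each.
- **Analysis.** Logistic regression of sero-positivity on age, sex, centrality (high or low) and environment (open or dense), with school mosquito density also included. No interaction and no four-level typology term is mentioned.
- **Total.** Section 5.1 sets 1000 children from 2 to 3 schools in each of the four area types.

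**The concern.** The formula's arms and the unit that receives its answer differ. By the protocol's definitions each arm is everyone at one level of one factor, and in a 2x2 layout each level contains two typologies. A requirement of 210 per level means about 105 per typology; the protocol asks for 210 per typology, which gives 420 per level. The site formula uses the same p0 and p1, so its answer is also per level although it is labelled per typology.

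A reader will take the stated power as that of the centrality and environment tests, and will read a null result against it. It is the power of a different comparison.

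The unit also decides what happens when other parts of section 9 are corrected. The Z of 0.84 corresponds to 80% power, not 90%. Using the 90% value raises n to 278. Applied per typology that is 4 x 278 = 1112 children, more than the planned 1000; applied per level it is 2 x 278 = 556.

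**Working it through.** **Inputs.** p0 = 0.26, p1 = 0.15, Z for alpha/2 = 1.96, Z for beta = 0.84, k = 0.6 to 1, 2 to 3 schools per typology, 1000 children (sections 9 and 5.1). Both formulas are read with the squared difference as divisor; the fraction bar appears to have been lost in text conversion.

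**1. Reproduce the protocol's figure.**
- Variance term: v = 0.26 x 0.74 + 0.15 x 0.85 = 0.1924 + 0.1275 = 0.3199.
- n = (1.96 + 0.84)^2 x 0.3199 / 0.11^2 = 7.84 x 0.3199 / 0.0121 = 207 per group.

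This matches the stated figure of about 210, as a two-group size at 80% power. With the Z for 90% (1.28) it is 278.

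**2. Identify the group.** The 26% and 15% approximate the one-factor pilot contrasts: high rates 27.1% and 25.2% (mean 26.2%), low rates 16.8% and 14.8% (mean 15.8%). The protocol states no school-level rates for the four crossed typologies. Definitions and inputs both point to factor levels, so n = 207 is per level, or about 104 per typology.

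**3. Power for each comparison, ignoring schools.** Power = Phi(0.11 / sqrt(0.3199/n) - 1.96), with n per group.

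| Comparison | n per group | Power |
|---|---|---|
| One typology vs another | 210 | 80.5% |
| One factor level vs the other, 210 per typology | 420 | 97.9% |
| One factor level vs the other, 1000 children | 500 | 99.2% |

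For example, at n = 420 the standard error is sqrt(0.3199/420) = 0.0276, 0.11/0.0276 = 3.99, and Phi(3.99 - 1.96) = 97.9%. Neither the 90% stated nor the 80% implied by 0.84 is the power of a main-effect test.

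An 11-point interaction (difference of differences, assuming cell rates of 26, 15, 26 and 15% for the variance) has about 51% power at 210 per cell and 58% at 250.

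**4. The same layout with school variation.** Two to three schools per typology are 4 to 6 per level. Solving the protocol's site formula for power with c schools per level and m children per school:

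Power = Phi(0.11 / sqrt([v/m + k^2(p0^2 + p1^2)] / (c - 1)) - 1.96), where p0^2 + p1^2 = 0.0676 + 0.0225 = 0.0901.

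| k | c = 4, m = 105 | c = 6, m = 83 |
|---|---|---|
| 0 | 93.2% | 97.7% |
| 0.6 | 17.1% | 25.2% |
| 1 | 9.1% | 12.4% |

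At k = 0.6 and c = 4, for instance: 0.3199/105 + 0.36 x 0.0901 = 0.0355; sqrt(0.0355/3) = 0.1088; 0.11/0.1088 = 1.01; Phi(1.01 - 1.96) = 17%. The k = 0 row lies below the table in step 3 because this formula uses c - 1 and because 6 x 83 = 498, not 500. The 8 x 105 = 840 layout is four typologies of 210 in two schools each; 105 is just above the protocol's 80 to 100 per school, and using 100 leaves the k = 0.6 and k = 1 entries at 17% and 9%.

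**5. Where the low power comes from.** Putting k = 0.6 and n = 210 into the site formula gives 1 + 7.84 x (0.3199/210 + 0.36 x 0.0901) / 0.0121 = 23 sites; k = 1 gives about 60. The stated two to three schools do not follow from the formula under either unit. Reading the design per level raises the number of schools per arm from 2-3 to 4-6, which increases power. The unit error is therefore not the cause of the low figures in step 4.

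**The case against.** The strongest reply is that 210 per typology is a deliberate, cautious choice. The summary's rationale makes the connectivity effect depend on environmental suitability, the principal objective refers to four environments, the expected results are stratified by four types, and section 5 describes the main aim as sero-prevalence in four types of area. For one type against another, 210 each gives about 80% power. This gives the four types some standing as units of interest, and section 9 lists model variables without excluding an interaction or cell contrasts. But on this reading p0 and p1 are misdefined and the rates are for the wrong groups, so the calculation still does not match its use.

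A second reply is that the slip is harmless. Its direction is: ignoring schools, each main effect gets twice the children the formula asks for. A reader might infer from the mismatch that too few children are planned, or that the 9 to 25% power under the protocol's k results from it. The documents do not support either. The individual-level number is more than sufficient, and the low power follows from a site calculation that does not yield two to three schools at k = 0.6 to 1. Nor is 210 itself miscalculated, since it reproduces to within 3%.

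**Conclusion.** The point stands as a unit error in section 9. A per-level sample size and a per-level site number are both stated per typology, and the quoted power does not describe the centrality or environment test in the stated model. Ignoring schools, the error is conservative: 97.9 to 99.2% for the main effects against 80.5% for the comparison that 210 versus 210 describes. Two neighbouring faults are separate: the 90% power paired with 0.84, and the site number that does not follow from k.

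The figures assume 26% against 15%, a two-sided 5% level, children and schools spread evenly over the four typologies, typology taken at the school, and the protocol's k applying within each factor level. It is worth correcting because the study's stated justification rests on it, but it is not a reason to change enrolment.

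**What to change.** In section 9:

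1. State that n and the site number are per level of centrality or of environment, and give what the design delivers: 420 to 500 children and 4 to 6 schools per level.
2. Restate the power of the two main-effect tests for that layout over the protocol's own range of k, rather than quoting one figure.
3. If a typology-versus-typology or interaction contrast is intended, name it, use rates for the typologies instead of factor-level rates, and include that term or contrast in the model.

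The cost is rewording and recalculation of one section, with no change in enrolment. The downside is that the restated power will look less favourable once school variation is carried through: about 17 to 25% at k = 0.6 and 9 to 12% at k = 1. The site-number calculation should be corrected at the same time.

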### **5.1. General organisation of the study**

#### **A. Sero-prevalence**

A one-time cross-sectional sero-prevalence study to measure IgG seropositivity will be performed in each of the selected schools in pupils aged 10-15 years old. The total number of participants in the research project is 1000. Collected from 2-3 schools in each of the four area types.

After consent to allow child participation, the pediatrician will use a rapid diagnostic lateral flow blood test to measure the immunity against dengue and chikungunya from the children. The blood sampling will be drawn from the fingertips for two drops (1 drop per test) at the child school. The result will be reported within the same day of the test. Parents will be required to answer the Dengue and Chikungunya questionnaires.

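### The sample size paragraph claims 90% power but uses Zbeta = 0.84, the 80% constant, so ~210 per typology is an 80% figure for one typology against another.

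*Protocol*

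**What the plan says.** Section 9 (Statistical considerations) bases the calculation on pilot seroprevalences of "approximately 26% vs 15" per cent and concludes: "we estimate a necessary sample size of ~210 children for each of the four typologies". The formula is the unpooled comparison of two proportions, introduced by "Where n is the required sample size per treatment arm". The first proportion is described as that of area type 0, "ie Central + or Environment" +, and the second as its Central – or Environment – counterpart.

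The constants follow the phrase "as acceptable and a study with 90% power, the following constant values are": Zalpha/2 = 1.96 and Zbeta = 0.84. The same two constants enter a second formula for the number of sites per typology. That formula takes n = 210 and a between-site coefficient of variation k of 0.6 to 1, and is said to lead to at least two and ideally three schools per typology, with 80 to 100 children in each.

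On planned enrolment, section 5.1.A says: "The total number of participants in the research project is 1000". Spread evenly over four area types, that is 250 each. No allowance for dropout is made. Little is needed, since section 8 gives participation as "1 day for seroprevalence study and questionnaire".

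**The concern.** The power label and the constant contradict each other within one sentence. The standard normal distribution function at 0.84 is 0.7995, so 0.84 belongs to 80% power; the value for 90% is 1.2816. Either the label or the constant is wrong, and the resulting n shows which one was used.

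The power applies to the principal evaluation criterion, seroprevalence by area type. A reader who sees 90% takes the chance of missing the assumed difference to be 10%, when the calculation allows about 20%. A null result for a typology contrast would then look stronger than the design warrants. This is a wrong figure stated in the protocol, not a detail that could be left to a statistical analysis plan.

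**Working it through.** **Inputs, all from section 9 unless noted**
- Two-sided alpha 0.05, Zalpha/2 = 1.96
- Zbeta = 0.84 as printed; 1.2816 for 90% power
- p0 = 0.26, p1 = 0.15
- Stated n of about 210 per typology
- Total enrolment 1000 (section 5.1.A), so 1000/4 = 250 per typology

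The division by (p0 − p1)² does not show in the extracted text of either formula. It is restored here and not counted as an error.

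**1. Reproducing the protocol's figure**

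n = (Zalpha/2 + Zbeta)² × [p0(1 − p0) + p1(1 − p1)] / (p0 − p1)²

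- Variance term: 0.26 × 0.74 + 0.15 × 0.85 = 0.1924 + 0.1275 = 0.3199
- Squared difference: 0.11² = 0.0121
- Zbeta = 0.84: 2.80² = 7.84, so n = 7.84 × 0.3199 / 0.0121 = 207.3

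This is the stated ~210, so the printed 0.84 is the constant that was used.

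**2. The same formula at 90% power**

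- Zbeta = 1.2816: 3.2416² = 10.508, so n = 10.508 × 0.3199 / 0.0121 = 277.8, or 278 per typology
- Over four typologies: 4 × 278 = 1,112
- Gap: 278 − 210 = 68, and 68/278 = 24%. Put the other way, 278 is 32% above 210.

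**3. Does another 90% calculation give 210?**

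| Variant at 90% power | n per group |
|---|---|
| One-sided alpha 0.05, unpooled | 227 |
| Two-sided, unpooled (the protocol's formula) | 278 |
| Two-sided, pooled variance | 281 |
| Two-sided, pooled, continuity-corrected | 299 |

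None does. At 80% power the two-sided pooled version gives 211, again close to the stated figure.

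**4. Power at the relevant sizes, children treated as independent**

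Power = Phi(0.11 / √(0.3199/n) − 1.96)

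| n per side | Where it comes from | Power |
|---|---|---|
| 210 | Stated need, one typology against another | 80.5% (pooled variance 80.0%) |
| 250 | 1000/4, one typology against another | 86.8% (pooled variance 86.4%) |
| 420 | 2 × 210, main effect pooled over two typologies | 97.9% (pooled variance 97.8%) |

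**5. The site-number formula**

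Sites = 1 + (Zalpha/2 + Zbeta)² × [p0(1 − p0)/n + p1(1 − p1)/n + k²(p0² + p1²)] / (p0 − p1)²

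With n = 210: 0.3199/210 = 0.00152, and p0² + p1² = 0.0676 + 0.0225 = 0.0901.

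- k = 0.6, Zbeta = 0.84: 1 + 7.84 × (0.00152 + 0.03244) / 0.0121 = 23.0
- k = 1, Zbeta = 0.84: 1 + 7.84 × (0.00152 + 0.0901) / 0.0121 = 60.4
- Zbeta = 1.2816: 30.5 and 80.6

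Putting 80 to 100 children per school in place of 210 changes little (about 24 to 62 at Zbeta = 0.84). Setting k to zero gives 1.99. With k at 0.6 to 1, neither value of Zbeta gives two or three sites.

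**The case against.** The strongest reply is that 210 per typology may be ample for the analysis actually planned. Section 9 describes the two proportions by level of centrality or environment, and the logistic model has centrality (high or low) and environment (open or dense) as separate factors. Each level of a factor pools two typologies, so the comparison is 420 against 420, with about 98% power under independence. This stands as far as it goes. A reader might infer from the wrong constant that the sample is simply too small for 90% power, and the protocol does not support that without condition. But the wording is mixed: n is defined per arm and then required for each of the four typologies, which is a typology-against-typology calculation, and that calculation gives 80%. On neither reading do 90%, 0.84 and 210 belong together.

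A second reply is that 210 is a minimum and more children are planned. This softens the gap without closing it. The planned 250 per typology gives about 87%. Three schools of 80 to 100 (240 to 300 children) would give about 85% to 92% under independence, but the upper end means 4 × 300 = 1,200 children, above the stated total. The two-school minimum (160 to 200 children) gives about 69% to 79%.

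A third reply is that this is a slip in one label, with no change to enrolment, endpoint or model. That is fair as to cost. It does not make the stated power right.

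**Conclusion.** The point holds in a limited form. The stated 90% is wrong for the calculation shown: ~210 per typology follows from the 80% constant, and 90% by the same formula needs 278, so 210 is about 24% short for one typology against another. This rests on the protocol's own 26% and 15%, two-sided alpha of 0.05, equal groups and independent children.

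Two stronger conclusions should not be drawn. One is that the study is too small in every respect: under independence, the pooled main effect has about 98% power at 420 per level. The other is that changing the label to 80% settles the power of the study. The 80% ignores school clustering, and section 9 itself reports a coefficient of variation of 0.6 to 1 between sites. Carried through the protocol's own site formula, that asks for about 23 to 60 sites per typology at Zbeta = 0.84, against the two or three planned. Correcting Zbeta does not repair that step; it is a separate and larger problem.

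**What to change.** In section 9:

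1. Replace 90% with 80% for the figure of 210 per typology. If 90% is to be kept for this contrast, use Zbeta = 1.28 and state 278 per typology, 1,112 in total, which is 112 more than the planned 1000.
2. State that the figure is for one typology against another and assumes independent children, with no allowance for school clustering. If the pooled main effect of centrality or environment is the intended contrast, say so and give its power separately.
3. Use the same Zbeta in the site-number formula, then recheck that formula and its inputs separately, because its printed form does not give two or three sites with either constant.
4. Until that is done, present neither 80% nor 90% as the power of the clustered design.

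Items 1 (with the 80% label), 2 and 4 cost a line or two of text and change nothing in the field; the stated power becomes less favourable. Item 3 needs a fresh calculation, and its result may bear on the number of schools.

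### At the between-school variation the plan states, its site-number formula gives 23 to 60 schools, not two to three, and power at that variation is far below the stated 90%

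*Protocol*

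**What the plan says.** Section 9 of the Protocol sizes the study in two steps.

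- Individuals: from pilot prevalences of about 26% and 15%, "we estimate a necessary sample size of ~210 children for each of the four typologies". The stated power is 90%, with Z values of 1.96 and 0.84.
- Sites: the pilot is said to show variation within the typologies ("coefficient of variation ranging from 0.6-1"), and a second formula carries that variation through a k-squared term. Its terms are defined thus: "Where k is the coefficient of variation and n the number of individuals as calculated above". The conclusion is that "we would need at least two and optimally three schools per environmental typology with 80-100 children per school".

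Section 5.1.A carries this into the design: "The total number of participants in the research project is 1000. Collected from 2-3 schools in each of the four area types". The summary and section 3.2 give the resulting total of 8 to 12 schools. The planned analysis in section 9 is a logistic regression with centrality and environment entered as separate explanatory variables.

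**The concern.** A k of 0.6 to 1 means that the standard deviation of true prevalence between schools is 60% to 100% of the mean. With variation that large, two or three clusters per group would rarely separate 26% from 15%, so the stated number of sites looked implausible beside its own inputs.

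The number matters because a school's centrality and environment are the same for every child in it. For the school typology, information on the primary association therefore comes mainly from the number of schools, and adding children within a school helps little. If the number of sites is wrong, readers and ethics committees are being told that 8 to 12 schools suffice when the plan's own calculation says otherwise.

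**Working it through.** **Inputs (all from section 9).** p0 = 0.26, p1 = 0.15, so (p0 − p1)² = 0.0121. p0(1 − p0) + p1(1 − p1) = 0.1924 + 0.1275 = 0.3199. p0² + p1² = 0.0676 + 0.0225 = 0.0901. (1.96 + 0.84)² = 7.84.

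**Step 1: reproduce the 210.** 7.84 × 0.3199 / 0.0121 = 207, in line with the stated ~210. This also settles the form of the formulas. No division sign is visible before (p0 − p1)² in the text at hand, possibly lost in reading the PDF, but 210 results only if that term is a divisor.

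**Step 2: the site formula with the stated inputs.** Sites = 1 + (7.84 / 0.0121) × [0.3199/n + k² × 0.0901], with n = 210:

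| k | Sites |
|---|---|
| 0 | 1.99 |
| 0.13 | about 3 |
| 0.6 | 23.0 |
| 1 | 60.4 |

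Two to three sites thus correspond to almost no variation between schools. Leaving the divisor out altogether gives 1.27 (k = 0.6) and 1.72 (k = 1), which round up to two. That may be the origin of the figure, but the document does not show it. One-sided testing (1.645 in place of 1.96) still gives 18 to 48. A Z of 1.28, as 90% power requires, gives 30.5 and 80.5; the mismatch between 90% power and 0.84 is a separate error.

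**Step 3: the n in the formula.** The formula adds up variance per site, so n should be children per school, not the typology total of 210. With n = 80 to 100 the results are 24.1 to 24.6 (k = 0.6) and 61.5 to 62.0 (k = 1), a small change.

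**Step 4: which contrast.** If each factor is tested pooled over the other, as the regression does, 23 to 60 is the number per factor level. Each level spans two typologies, so the need per typology is about 12 to 30. Against the larger planned figure of three, that is at least fourfold.

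**Step 5: power of the planned design.** Take 12 schools with 1000/12 = about 83 children each. Invert the formula for c schools per group: z = 0.11 × √[(c − 1)/V] − 1.96, with V = 0.3199/83 + k² × 0.0901.

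| k | V | Pooled, c = 6 | Single typologies, c = 3 |
|---|---|---|---|
| 0.2 | 0.0075 | 81% | not computed |
| 0.6 | 0.0363 | 25% | 13% |
| 1 | 0.0940 | 12% | 7% |

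For example, at k = 0.6 and c = 6, 0.11 × √(5/0.0363) − 1.96 = −0.67, which is 25% power. Using c in place of c − 1 raises the pooled figures only to 29% and 14%.

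**Step 6: the two-school minimum.** Two schools of 80 to 100 give 160 to 200 children, below the 210 called necessary, and eight such schools give 640 to 800 in all. Three schools give 240 to 300 per typology and 960 to 1200 in all, consistent with the planned 1000.

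**The case against.** The strongest reply is that low power has not been shown, because the true k may be much smaller than the pilot suggests. This stands. The protocol does not say how many pilot children each school contributed, but small numbers alone could produce such values. At an assumed prevalence of 20%, binomial noise gives a coefficient of variation of √(0.8/(0.2m)), which is 0.6 with m = 11 children and 1.0 with m = 4, even with no true difference between schools. The pilot also covered ages 3 to 15, with seroprevalence of 6.5% at 3–9 years and 37.2% at 10–15, so differing age mixes could inflate k. The study enrols only ages 10 to 15 and adjusts for age.

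A reader might therefore infer from the arithmetic that the design is simply underpowered, or that a null result could not be interpreted at all. The documents support neither. The shortfall follows only if k is as stated, and an estimate with an interval that reflects variation between schools would still be informative.

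A second reply is that 23 to 60 per typology overstates the need for a main-effects model. That also stands, and the pooled figures are the ones to lead with.

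Neither reply rescues the sentence itself. It says that k of 0.6 to 1 was used and led to two or three schools, and it did not. Nor does it help that the regression as described names no school term: near-nominal power would then come only from ignoring the variation that the plan quotes.

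**Conclusion.** The stated number of sites is wrong as written. From the plan's own inputs the formula gives 23.0 to 60.4 schools, or about 12 to 30 per typology when each factor is pooled over the other, against two to three. At the stated k, 12 schools of about 83 have roughly 25% to 12% power for a pooled factor and 13% to 7% for a contrast of single typologies. The plan states 90%, and the Z it uses corresponds to 80%.

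The arithmetic needs no assumption beyond reading (p0 − p1)² as a divisor, which the 210 requires. The power figures assume a normal approximation, equal school sizes, prevalences of 26% and 15%, and k as stated. If k is really near 0.2, the pooled contrast would be adequately powered at about 81%, but the plan would then have to say so and justify it.

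**What to change.** In section 9:

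1. Replace the concluding sentence with the formula's correct output, using children per school for n.
2. Re-estimate k from the pilot after removing binomial sampling noise and differences in age mix, and report how it was done.
3. State the power or detectable difference of the actual design (12 schools of about 83) over the plausible range of k. Call the typology contrast exploratory if power stays low.
4. Delete the two-school minimum and fix three schools per typology, here and wherever 2–3 or 8–12 schools appears. This is within the stated range and reaches 210.

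The cost is a less favourable power statement and the loss of the two-school fallback; no children are added to the planned 1000.

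Spreading the same children over more schools is an option for the sponsor to weigh, not a requirement. Each added school also needs traps monitored weekly for a year (section 5.1.B). Even all 34 listed schools with 30 children each, assuming 17 per factor level, would reach only about 56% at k = 0.6 (0.11 × √(16/0.0431) − 1.96 = 0.16) or 28% at k = 1.
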